## Abstract

Hybrid trials that include both clinical and implementation science outcomes are increasingly relevant for public health researchers that aim to rapidly translate study findings into evidence-based practice. The DeWorm3 Project is a series of hybrid trials testing the feasibility of interrupting the transmission of soil transmitted helminths (STH), while conducting implementation science research that contextualizes clinical research findings and provides guidance on opportunities to optimize delivery of STH interventions. The purpose of DeWorm3 implementation science studies is to ensure rapid and efficient translation of evidence into practice. DeWorm3 will use stakeholder mapping to identify individuals who influence or are influenced by school-based or community-wide mass drug administration (MDA) for STH and to evaluate network dynamics that may affect study outcomes and future policy development. Individual interviews and focus groups will generate the qualitative data needed to identify factors that shape, contextualize, and explain DeWorm3 trial outputs and outcomes. Structural readiness surveys will be used to evaluate the factors that drive health system readiness to implement novel interventions, such as community-wide MDA for STH, in order to target change management activities and identify opportunities for sustaining or scaling the intervention. Process mapping will be used to understand what aspects of the intervention are adaptable across heterogeneous implementation settings and to identify contextually-relevant modifiable bottlenecks that may be addressed to improve the intervention delivery process and to achieve intervention outputs. Lastly, intervention costs and incremental cost-effectiveness will be evaluated to compare the efficiency of community-wide MDA to standard-of-care targeted MDA both over the duration of the trial and over a longer elimination time horizon.

## Introduction

On average it takes over a decade for clinical research to translate into effective policy and evidence-based practice [1]. However, there is an increased understanding that systematic assessments of the delivery systems, processes, and policies that contextualize clinical research findings are necessary for ensuring that data are relevant and meaningfully adapted to different epidemiological and implementation contexts. In particular, the success of neglected tropical disease (NTD) programs that utilize mass drug administration (MDA) of preventative chemotherapies are highly reliant upon strong distribution channels that facilitate programs achieving high treatment coverage of targeted populations. Given global control and elimination targets outlined in the World Health Organization (WHO) NTD Roadmap and 2012 London Declaration, effective and efficient delivery of MDA programs with high coverage and scale is critical [2].

There are a number of factors that influence MDA coverage in the delivery of routine programs, including drug supply chains, population enumeration, human resource availability and capability, and social sensitization and mobilization. These, in addition to other factors, can be systematically studied through implementation science (IS), which is the scientific practice of identifying, testing and scaling up effective interventions with high quality, fidelity and efficiency. IS is increasingly relevant within NTD programs to ensure that innovations and tools reach populations in need and are appropriately adapted to the local context while maintaining core elements of proven interventional strategies [3]. Applying these methods requires multidisciplinary approaches to studying the process of implementation and the translation of findings into practice. Using IS tools to assess opportunities, address challenges and optimize innovative approaches to NTD control and elimination programs is inherently important and, in light of the Sustainable Development Goals, promotes strong public health delivery systems in NTD-endemic countries [4].

Clinical trials that incorporate implementation or operational research questions are referred to as hybrid studies [5]. The DeWorm3 Project was launched in 2016 as a series of large hybrid trials in Benin, Malawi, and India. The purpose of these trials is to test the feasibility of interrupting the transmission of soil transmitted helminths (STH) using expanded chemotherapeutic approaches while concurrently generating information on the opportunities, challenges, and best-practices for delivering novel STH transmission interruption programs. DeWorm3 aims to preemptively bridge the “know-do” gap by using IS methods to speed the evidence translation process needed to inform STH elimination guidelines, public health practice, and policies and operational plans. By embedding rigorous IS methods within DeWorm3, we aim to (1) describe the implementation environment that contextualizes clinical research findings, and (2) if interventions are found to be efficacious, to generate evidence regarding effective strategies for promoting and scaling-up the interventions to interrupt transmission. This research builds and expands upon prior NTD implementation research from Uganda [6, 7] and Kenya [8, 9] including the ongoing work by the Tumikia project, another randomized trial evaluating the impact of intensified deworming on hookworm transmission [10].

### Aims and objectives

DeWorm3 is a series of cluster randomized trials evaluating the feasibility of interrupting transmission of STH using biannual (twice annually) community-wide MDA targeting eligible community members of all ages. Additionally, DeWorm3 aims to assess the relative influence of community-wide MDA on STH prevalence and transmission intensity as compared to standard-of-care targeted MDA. The rationale, objectives, and design of the DeWorm3 Project clinical trial are described elsewhere in this supplement [11].

The effectiveness of community-wide MDA for STH is driven in part by epidemiological factors (baseline disease prevalence and STH species distribution), intervention characteristics (drug efficacy), systems factors (health system strength), and social factors (community member beliefs and preferences) that influence intervention acceptability, penetration, and uptake. These factors are highlighted in the DeWorm3 theoretical model (Fig 1). The overall objective of DeWorm3 IS research is to evaluate these factors in order to develop and test a community-wide STH MDA model that is sustainable and scalable in STH-endemic areas. Specific research aims include:

To systematically identify stakeholders influencing standard of care targeted and community-wide MDA and map their potential role and involvement in scale-up of community-wide MDA for STH.To identify implementation-related barriers and facilitators to community-wide MDA for STH from the perspective of various stakeholders:
At baseline, to identify barriers and facilitators (i.e. lessons learned) from other community-wide MDA programs, such as lymphatic filariasis (LF) and school-based STH programs, in order to optimize delivery of community-wide MDA for STH.At midline and endline, to assess barriers and facilitators influencing delivery of community-wide MDA for STH and how these barriers and facilitators vary across clusters achieving high and low treatment coverage.To quantify the readiness of the health system to deliver community-wide MDA for STH programs:
At baseline, to identify readiness to deliver community-wide MDA for STH programsAt endline, to identify readiness to scale-up community-wide MDA for STH programs and assess changes in readiness over time.To map the intervention delivery process and identify any discrepancies between planned and implemented activities in order to optimize the trial intervention.To compare the financial and economic costs and incremental cost-effectiveness of community-wide and targeted MDA for STH in the short- and long-term:
To compare the costs and incremental cost-effectiveness of providing six biannual rounds of community-wide MDA versus three annual rounds of targeted standard of care MDA program in each study country.To compare the costs and incremental cost-effectiveness of interrupting STH transmission using a community-wide MDA platform versus a targeted standard of care MDA program in each study country.

**Fig 1 pntd.0005988.g001:**
[figure not shown]
DeWorm3 theoretical model depicting system of influence on successful community-wide MDA delivery.

## Methods

IS research will be conducted at DeWorm3 baseline (i.e. formative research), midline (i.e. process research), and endline (i.e. summative research). The purpose of conducting formative research is to strengthen DeWorm3 implementation by preemptively identifying implementation barriers and facilitators, seeking support from influential “gatekeepers,” and building consensus. Stakeholder analysis, qualitative data collection, and readiness assessments will contribute to formative research, as described below. Process research will provide important information regarding the contextual factors such as intervention acceptability, uptake, and penetration that influence observed DeWorm3 trial outcomes. Qualitative data collection and process mapping activities will contribute to process research. Lastly, summative research will be used to link implementation factors to key DeWorm3 outcomes (i.e. reductions in prevalence and achievement of transmission interruption) and evaluate how DeWorm3 interventions can be scaled, sustained, or translated into meaningful guideline recommendations. Qualitative data collection, readiness assessments, process mapping, and cost-effectiveness analyses will contribute to summative research. By tracking key implementation factors from baseline and continuously throughout the study, we will be able to identify how the DeWorm3 implementation landscape changes over the duration of the trial.

### Stakeholder analysis

Stakeholder analyses will be conducted in each DeWorm3 trial site at baseline (pre-launch), following trial launch, and at study endline. The purpose of the stakeholder analysis is to identify the individuals who influence or are influenced by effective targeted MDA and community-wide transmission interruption efforts and understand how the network dynamics may influence study outcomes and future policy development. A social network analysis strategy will be used to characterize the relationships between stakeholders in order to (1) describe and map members of the network, (2) characterize the relationship between the network members, and (3) analyze the network using standard network measures such as density, centrality, and homophily [12].

#### Data collection and analysis

A standardized stakeholder mapping exercise will be implemented in all DeWorm3 sites. In the first part of the exercise, working groups composed of the DeWorm3 IS team, personnel from Ministries of Health and Education, and local community-based organizations (CBOs) will identify and describe an exhaustive network of stakeholders who influence or are affected by school-based MDA and, separately, community-wide MDA for STH (adapted from [13]). Working groups will identify stakeholders at each level of the health system, including: the national level; state/regional (or equivalent) level; district (or equivalent) level; local/health center level; community level, including community drug distributors (CDDs), community leaders, and community members; and groups external to the government, including CBOs, non-governmental organizations (NGOs), or international bodies such as WHO.

The stakeholder mapping tool guides the systematic identification of a stakeholder’s influence on the outcomes of the intervention, their attitude towards the intervention, and opportunities to engage the stakeholder throughout the duration of DeWorm3 trial. Additional stakeholders might be added to the network at two follow-up time points, and their attitudes towards the intervention will be updated over time to document changing acceptability of the intervention. During the second part of the exercise, DeWorm3 staff will map the relational power dynamics and dependences between the stakeholders identified by characterizing the directionality of influence (i.e. who influences who) between the stakeholders and the influence category, including: supervision, financial support, technical support, or communication only.

De-identified stakeholder maps in which stakeholder names and affiliations have been removed will be analyzed using standard network measures to understand if: there are stakeholders with extensive influence (i.e. degree centrality), there is high interconnectedness across stakeholders, there are stakeholders who link the network together (i.e. between centrality), there is density around specific stakeholders that might hinder sustainability, there is integration across government ministries and external organizations, or if there is the potential for dysfunctional relationships that might influence intervention effectiveness [12]. Over the duration of the DeWorm3 trials, stakeholder maps will also be used to explore the association between stakeholder attitudes and effective implementation in relevant geographic areas in order to understand if high intervention acceptance of influential stakeholders has a cascade effect at other levels, thereby positively influencing treatment coverage.

### Qualitative research

Qualitative research will be conducted at trial baseline, midline, and endline to identify factors influencing implementation quality, feasibility, and sustainability by site. Qualitative research will utilize the Consolidated Framework for Implementation Research (CFIR) as a guide for data collection and analysis. The CFIR is a validated tool utilized in the United States and increasingly in low- and middle-income countries [14, 15]. The CFIR is built upon a number of preexisting implementation theories to provide a comprehensive meta-theoretical framework of 39 “constructs” that influence implementation [16]. Application of the CFIR helps guide theory development and verify whether and why interventions work through the identification of core and modifiable intervention characteristics [17].

CFIR constructs are organized according to five major domains influencing implementation effectiveness including: (1) the intervention, (2) the inner setting, (3) the outer settings, (4) the individuals involved, and (5) the process of undertaking the intervention. The “intervention” is defined as the core characteristics of the planned intervention. The “inner and outer settings” comprise the contexts where the implementation activities will occur. The “individuals involved” are the agents of change, those who have power and influence to seek, experiment with, or evaluate interventions. Lastly, the implementation process describes an active progression towards attaining the outcome of the intervention described [18]. We have selected a subset of 21 constructs to assess according to the following salience criteria: (1) is the construct a potential barrier or facilitator to community-wide MDA for STH? and (2) Would the construct exhibit heterogeneity across stakeholder groups or clusters? Question guides are designed to address the targeted constructs and are tailored to the stakeholder level (i.e. national, district, etc.). Baseline qualitative research will help refine CFIR construct selection for use during process and summative research as well.

#### Data collection and analysis

Focus group discussions (FGDs) and individual interviews will be conducted with stakeholders from all levels of the health system. FGDs with cluster-level stakeholders will take place in four randomly selected clusters per site, including community members, CDDs, and health center staff or CDD supervisors. FGD participants will be selected using random purposive sampling [19]. Interviews will take place with individuals at higher levels of the health system. These individuals will be selected using purposive quota sampling of mutually exclusive key informant groups (i.e. stakeholder levels) [20].

Trained interviewers who are fluent in local language and customs will conduct one-on-one interviews and small FGDs in private locations with consenting individuals. The interviews will be semi-structured key informant interviews with a mix of respondent and informant style questions. In each site, we use pragmatic criterion to determine the sample size, influenced by the number of levels of the site’s health system. If it is deemed that data saturation has been achieved and redundancy criterion are met within a given stakeholder group after 80% of interviews have been conducted in that group, the sample size may be reduced.

All interviews will be audio recorded and transcribed. Transcriptions will be translated to English. Two primary coders will independently code the site-specific transcripts using CFIR sub-constructs as analysis guides and coordinate their coding to create a comprehensive codebook and thematic analysis. Analyses will be based upon a deductive approach[21]. Special attention will be paid to distinguish factors related to the content and structure of the intervention, opportunities to enhance fidelity of the intervention, penetration within the health system, and opportunities to bring the intervention to scale. Similarities and differences in identified factors will be assessed within and across sites, leveraging the inherent heterogeneity present across clusters.

At midline and endline, qualitative research at the cluster level will take place in four randomly selected clusters per site: two high coverage clusters (80–100% average treatment coverage in year 1) and two low/moderate coverage clusters (<80% average treatment coverage in year 1). CFIR constructs will provide a framework for understanding why the DeWorm3 intervention may exhibit differential effectiveness across settings, correlates of high coverage, and opportunities to optimize the intervention moving forward. Following thematic coding, two independent analysts will assign scores to data at a cluster level to distinguish CFIR constructs that are missing too much data (M), do not distinguish between coverage levels (0), weakly (+1/-1), or strongly (+2/-2) distinguish coverage levels. The ratings reflect the positive or negative influence (valence) and strength of each construct on influencing implementation [18]. These relationships will be evaluated using chi-square tests. Findings will be synthesized to develop recommendations for best practices and highlight barriers and facilitators of implementation in high and low coverage sites.

Quality control will be ensured through a process of (1) random one minute spot checks of each transcribed audio file at a site level, (2) coding review and confirmation of 10% of coded transcripts from each site at the central DeWorm3 level, and (3) coding review and confirmation of 5% of coded transcripts between sites (i.e. circular quality assurance).

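### The 0/±1/±2 construct score has two incompatible definitions, one of which already contains the coverage comparison that the chi-square test appears meant to assess

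*Protocol article*

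**What the plan says.** In the protocol article, under Qualitative research, Data collection and analysis, midline and endline cluster-level work takes place in four clusters per site. Two have year-1 average coverage of 80–100% and two have less than 80%. The purpose is to understand "why the DeWorm3 intervention may exhibit differential effectiveness across settings, correlates of high coverage", among other things.

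The scoring is then set out in three consecutive sentences:

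1. After thematic coding, "two independent analysts will assign scores to data at a cluster level to distinguish CFIR constructs" that have too much missing data (M) or that "do not distinguish between coverage levels (0), weakly (+1/-1), or strongly (+2/-2) distinguish coverage levels".
2. "The ratings reflect the positive or negative influence (valence) and strength of each construct on influencing implementation".
3. "These relationships will be evaluated using chi-square tests".

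The findings are then synthesised into best-practice recommendations and into barriers and facilitators for high and low coverage. The article selects 21 constructs and says baseline work may refine that choice.

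**The concern.** One set of codes carries two meanings. In the first sentence, 0, ±1 and ±2 record how well a construct separates high from low coverage. In the second, they record the direction and strength of its influence on implementation. These are different quantities, made at different stages and from different information. Two teams following the text could produce data sets that cannot be combined.

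The first meaning has a further consequence. Nobody can say that a construct strongly distinguishes coverage levels without knowing which clusters are high and which are low. If the score is then tested against coverage, the test examines a comparison the raters have already made. At stake is the answer to the second research aim, on how barriers and facilitators differ between clusters with high and low coverage. Recommendations resting on such scores could reflect what raters expected of a well or poorly covered cluster.

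**Working it through.** The article gives no sample size, power or error rate for this analysis, so there is no figure to reproduce. The check is a reading of the text, followed by an illustration of size.

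**Reading the definitions**

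| | First definition | Second definition |
|---|---|---|
| What the code states | Whether a construct separates coverage levels | Direction and strength of influence |
| Natural unit | One construct, compared across clusters | One construct in one cluster |
| Needs the coverage class? | Yes | No |
| Test against coverage | Adds no valid information | Can inform, if ratings do not depend on known coverage |

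The text says that "two independent analysts will assign scores to data at a cluster level". A cluster has one coverage class, so a score for one cluster cannot express separation between classes. The first definition therefore does not fit the stated unit, while the second does.

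The article does not name the variable against which scores are tested. Three things point to coverage: the clusters are sampled on it, the first definition refers to it, and the stated purpose is to find its correlates.

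**Illustration under the second definition**

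Inputs from the article: 2 high and 2 low/moderate clusters per site. Assumptions of this review: ratings are reduced to favourable or unfavourable, clusters are rated independently, and the construct has no true relation to coverage. Let q be the probability that a cluster is rated in the direction its known coverage would suggest (favourable if high, unfavourable if low). With no influence of coverage, q = 0.5. The article gives no value of q, so 0.7 and 0.8 only show a range.

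Perfect separation in one site, in either direction, has probability q⁴ + (1 − q)⁴:

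- q = 0.5: 0.0625 + 0.0625 = 0.125
- q = 0.7: 0.2401 + 0.0081 = 0.248
- q = 0.8: 0.4096 + 0.0016 = 0.411

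The second term is separation in the unexpected direction. It falls from 0.0625 to 0.0081 and 0.0016, so the rise comes entirely from the expected direction.

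**Pooled over sites**

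Assuming one site in each of the three countries, there are 6 high and 6 low clusters. Summing exact binomial probabilities over all possible 2×2 tables, at an assumed two-sided 0.05 level, gives these rejection rates for the same unrelated construct:

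| q | Pearson chi-square, no continuity correction | Fisher exact |
|---|---|---|
| 0.5 | 5.8% | 0.6% |
| 0.7 | 29.7% | 8.5% |
| 0.8 | 60.1% | 27.5% |
| 1.0 | 100% | 100% |

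**A separate limit**

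Within one site, a fully separated 2 v 2 table has every expected count equal to 1. Its uncorrected Pearson p-value is 0.046, but the Fisher p-value is 0.33. The 12.5% baseline reflects having four clusters, not rater bias. Better scoring does not cure that.

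**The case against.** The strongest defence is that the two sentences describe two stages in compressed form: analysts rate each cluster for valence and strength, then compare ratings across coverage groups, and the distinguishing labels are the result. The cluster-level unit and the second sentence support this, and the text cites a source for the method. On that reading nothing is circular, and what remains is silence on masking, which a condensed article may leave to the full protocol.

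Part of this stands. Silence on masking is not an error in itself, and the two-stage reading is a sensible account of the intention. But the article does not state it. It attaches the distinguishing labels to the scores the analysts assign, and reuses the same codes for valence and strength. That is a conflict in what is written. Independence between the analysts does not settle it, since both can know the coverage class. The listed quality control covers transcription and coding, not scoring.

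A reader might go further and infer that every non-zero score is guaranteed to be associated with coverage. The documents do not support that. A cross-cluster verdict gives one value per construct, which cannot be cross-tabulated with cluster coverage, so there is no test whose result could be guaranteed. A code of ±1 means only weak separation. And the test's second variable is inferred.

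It is also fair that 0.7 and 0.8 are invented values, that the real scale has more than two categories, and that recommendations also draw on the thematic analysis, while process mapping studies coverage separately.

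**Conclusion.** The concern holds in this form: the score has two incompatible definitions, and one of them builds in the comparison that the chi-square test seems intended to make. Under that definition, testing against coverage gives no valid information. Under the other, the test can be informative, but ratings made with coverage known may be biased towards expectation. With assumed q of 0.7 or 0.8, perfect separation of an unrelated construct in one site rises from 12.5% to about 25% or 41%. These figures show sensitivity; they do not estimate the bias in this study.

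The conclusion rests on coverage being the second variable in the test, which is the natural reading but is not stated. Severity is moderate. This is an exploratory qualitative sub-analysis that feeds best-practice recommendations, and no trial endpoint depends on it.

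**What to change.** Write the scoring as two separate steps.

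1. The two analysts rate each construct in each cluster for valence and strength (−2 to +2, or M), working from transcripts without the cluster's coverage class. The agreed ratings are locked.
2. Only then is the coverage class merged in. Each construct is labelled as not, weakly or strongly distinguishing by a rule set before scoring and applied to the locked ratings, for example the difference between the high and low cluster ratings within each site. The rule should say how M ratings are handled.

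Name coverage class as the comparison variable. Present the within-site comparison descriptively, since two against two clusters cannot support a chi-square test whichever way the scores are made.

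The cost is revised wording and a file-handling step, with the same two analysts and no new data. It must be in place before scoring, because raters who have seen the coverage class cannot be masked afterwards. The downside is that masking will be imperfect: transcripts may hint at coverage. Recording whether the analysts could guess the class would show how far this matters.

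### Chi-square tests of cluster-level CFIR scores rest on two high- and two low/moderate-coverage clusters per site, too few for the chi-square reference distribution whether run per site or pooled

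*Protocol article*

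**What the plan says.** The text is in the protocol article under Methods, Qualitative research, Data collection and analysis.

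- **Sample.** Cluster-level work at midline and endline takes place in "four randomly selected clusters per site: two high coverage clusters" and two low/moderate-coverage clusters, divided at 80% average treatment coverage in year 1.
- **Unit of scoring.** After thematic coding, "two independent analysts will assign scores to data at a cluster level".
- **Scale.** A construct is marked M if too much data is missing. Otherwise it may "do not distinguish between coverage levels (0), weakly (+1/-1), or strongly (+2/-2) distinguish coverage levels", which gives five ordered values from -2 to +2.
- **Test.** "These relationships will be evaluated using chi-square tests". No exact version, continuity correction, pooling rule or significance level is given.

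Earlier in the same section, on the thematic coding, the article says: "Similarities and differences in identified factors will be assessed within and across sites". Under Qualitative research it selects 21 constructs. The Introduction places the trials in three countries.

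**The concern.** The chi-square test takes its p-value from a large-sample distribution. Here the independent unit is the cluster, and there are four per site, or twelve if three sites are pooled. With so few units the statistic can take only a handful of values, and the continuous reference curve need not match their true probabilities. The nominal 5% level is then not the real one, and the error can go either way depending on how many score values are used.

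Comparing barriers and facilitators between high- and low-coverage clusters is a stated aim of the implementation research. This is the only formal test named for the CFIR scores, and the findings go into the best-practice recommendations. A poorly calibrated p-value could give a construct more or less weight than four or twelve clusters can support.

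**Working it through.** The plan gives no power, sample-size or p-value figure for this test, so there is nothing to reproduce. Inputs from the article are 2 v 2 clusters per site, five score values, and three countries. Assumptions are one score per construct per cluster, one site per country (6 v 6 pooled), and a two-sided 0.05 level.

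**1. Expected counts.** A 2 x 5 table has 10 cells. The mean expected count is 4/10 = 0.4 for one site and 12/10 = 1.2 pooled. With two score values evenly split, each expected count is 2 x 2/4 = 1 for one site and 6 x 6/12 = 3 pooled.

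**2. One site, full separation** (for example both high clusters +2, both low clusters -2).
- Uncorrected Pearson: four cells each contribute (difference 1)²/1, so X² = 4 on 1 df and p = 0.0455.
- Exact: there are C(4,2) = 6 ways to label two clusters as high, and 2 are this extreme, so p = 2/6 = 0.333. No 2 v 2 layout can give a smaller two-sided exact p.
- Yates-corrected: X² = 1, p = 0.317.
- If the separated scores occupy three values, X² = 4 on 2 df and p = 0.135. If four values, X² = 4 on 3 df and p = 0.261.

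**3. One site, real false-positive rate.** From step 2, the uncorrected test falls below 0.05 only when both high clusters share one score and both low clusters share a different one.
- Two values with probabilities p and q: rate = 2p²q².
  - 50/50: 2 x 0.25 x 0.25 = 0.125
  - 70/30: 2 x 0.49 x 0.09 = 0.088
  - 80/20: 2 x 0.64 x 0.04 = 0.051
  - 90/10: 2 x 0.81 x 0.01 = 0.016
- k equally likely values: rate = k(k-1)/k⁴ = (k-1)/k³.
  - k = 2: 1/8 = 0.125
  - k = 3: 2/27 = 0.074
  - k = 5: 4/125 = 0.032

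In the worst case of 21 null constructs, all two-valued and evenly split, the expected number of false positives per site and time point is 21 x 0.125 = 2.6, against 21 x 0.05 = 1.05 nominally.

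**4. Pooled, 6 v 6.** All 2 x k tables were enumerated under a common score distribution, with df = occupied values minus 1.

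| Score distribution | Rate at nominal 5% |
|---|---|
| two values, 50/50 | 5.8% |
| two values, 70/30 | 6.8% |
| two values, 80/20 | 5.3% |
| two values, 90/10 | 1.7% |
| three equal | about 6.5% |
| five equal | 1.8% |
| five, 40/30/15/10/5 | 2.6% |

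**5. A pooled table where the verdict changes.** Take 5/1 v 1/5.
- Pearson: X² = 12 x (5x5 - 1x1)²/(6x6x6x6) = 12 x 576/1296 = 5.33, p = 0.021.
- Fisher: 2 x (6x6 + 1)/C(12,6) = 74/924 = 0.080.

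**6. What an exact test stratified by site can reach.** Permuting labels within each of three sites gives 6 x 6 x 6 = 216 arrangements. The smallest two-sided p is 2/216 = 0.009.

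**The case against.** **The per-site reading is not fixed.** The sentence about assessing factors within and across sites concerns the thematic coding and comes before the scoring step. It does not settle how the chi-square tests are run. This stands, so the per-site figures are conditional on that reading.

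**The value 0.046 is a special case.** It needs an uncorrected statistic, a single site and exactly two score values. Yates correction gives 0.317, close to the exact 0.333, and three or four occupied values give 0.135 or 0.261. This also stands. But the article does not mention a correction, and Yates is not available once more than two score values occur.

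**Pooled, the damage is modest.** True for average error rates, as step 4 shows. It does not protect individual constructs, as step 5 shows.

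**The article is condensed.** Details such as an exact variant may sit in a fuller plan. That would answer a complaint about missing detail. Here the article names both the test and the cluster count, and the two do not fit together.

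**Two stronger readings are not supported.** A reader might infer that chance yields a significant within-site result one time in three. That figure is conditional on the four scores splitting 2-2; the unconditional rate is at most 12.5%. A reader might also infer that these tests alone decide which barriers and facilitators are reported. The article attaches no decision rule to them and synthesises findings from the coding and ratings as well.

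**More observations might be counted.** Treating the two analysts' scores or the 21 constructs as separate observations would enlarge the table but add no independent clusters.

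**Conclusion.** The concern holds in a limited form. The stated test does not suit the stated number of clusters, per site or pooled. Per site and uncorrected, it can print p = 0.046 where no valid two-sided test can go below 0.33. Its real error rate then runs from 12.5% (two evenly split scores) down to 3.2% (five equal scores), and lower for a very uneven two-way split. Pooled, it is mildly liberal for two or three reasonably balanced scores and conservative for five, and borderline verdicts can change.

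This rests on one score per construct per cluster, a two-sided 0.05 level and, for the pooled figures, one site per country. None of these is stated outright. Severity is minor to moderate: the component is exploratory, but it feeds the best-practice recommendations.

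**What to change.** Replace the chi-square sentence with wording to this effect: for each construct, one exact permutation test is done, pooled over sites, on one consensus score per cluster. The statistic is the high-minus-low difference in mean score, and high/low labels are permuted within site. Clusters scored M for a construct are left out of that construct's test and the remaining labels are permuted. Within-site ratings are displayed descriptively, without p-values.

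With three complete sites this uses 216 arrangements. Each M reduces the number: one M in one site leaves 3 x 6 x 6 = 108. The count should therefore be reported with each p-value.

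The cost is a short change of wording and a few lines of code, with no new data. Within-site p-values are given up, but with 2 v 2 clusters no valid two-sided one could fall below 0.33.
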